### Assessment and outcome measures

Data will be collected to inform the primary and secondary outcome measures in the definitive trial (see Table 1). The proposed primary outcome measures include symptom severity, complications and requirement for treatment escalation, and the proposed secondary outcomes include change in anxiety, depression, sleep and quality of life as well as relapse to GHB/GBL use or change in other illicit drug or alcohol use 30 days after the start of detoxification.

**Table 1 Tab1:** Assessment schedule of quantitative measures

Assessment	Baseline or as soon as data can be obtained	Daily during detoxification			Last day of detoxification or next working day	Ad hoc	30 days post start of detoxification
		Inpatient	Weekday outpatient	Weekend outpatient			
CIWA-Ar	✓	✓	✓	✓	✓		
Sedation Assessment Tool	✓	✓	✓	✓			
Depression (PHQ-9)	✓				✓		
Anxiety (GAD-7)	✓				✓		
Sleep pattern questionnaire	✓	✓	✓	✓	✓		
Vital signs	✓						
Psychiatric history	✓						
Relevant past medical history	✓						
Concomitant prescribed medication	✓	✓	✓	✓	✓		
Lifetime GHB/GBL use questionnaire					✓		
Daily drug/alcohol/nicotine use questionnaire	✓	✓	✓	✓			
Time-life follow-back of alcohol and drug use					✓		
AUDIT (alcohol)					✓		
Treatment Outcome Profile					✓		
Client Satisfaction Questionnaire (CSQ-8)					✓		
Adverse events		✓	✓	✓		✓	
Expected events associated with GHB/GBL withdrawal						✓	
Protocol deviations						✓	
Follow-up GHB/GBL use questionnaire							✓
Follow-up drug/alcohol use questionnaire							✓
Follow-up service use questionnaire							✓

*AUDIT* Alcohol Use Disorders Identification Test, *CIWA-Ar* Clinical Institute Withdrawal Assessment for Alcohol, *GAD-7* Generalised Anxiety Disorder-7, *GBL* gamma-butyrolactone, *GHB* gamma-hydroxybutyrate, *PHQ-9* Patient Health Questionnaire-9

On the first day of GHB/GBL detoxification, ratings will be obtained from each participant of their symptoms of GHB/GBL withdrawal using a scale widely used for alcohol withdrawal – the Clinical Institute Withdrawal Assessment for Alcohol (CIWA-Ar) which is currently used clinically by teams to monitor GHB/GBL withdrawal [32–35]. The CIWA-Ar may not adequately capture all neuropsychiatric symptoms/signs [32, 33] and the Sedation Assessment Tool (SAT) will assess behavioural disturbance [36]. Depressive (Patient Health Questionnaire-9 (PHQ-9); [37]) and anxiety (Generalized Anxiety Disorder-7 (GAD-7); [38]) symptoms will be assessed using scales that are already in routine clinical use. We will also record sleep pattern using a questionnaire [39]. Any medication taken by the time of the ratings will be recorded. Blood pressure, respiratory rate, oxygen saturation and pulse will also be recorded when the CIWA-Ar is completed. Since this is a pragmatic trial, we aim to minimise any extra tests or investigations and research participants will receive standard medical care as usual. If, as part of this standard medical care, blood and/or urine will be collected for toxicological screening for recreational drugs/novel psychoactive substances, the results will be recorded but not sought solely for the purposes of this study.

During detoxification, daily assessments will record the withdrawal assessment scale (CIWA-Ar; [29]), behavioural disturbance (SAT; [36]), sleep pattern, any use of other drugs/novel psychoactive substances/alcohol and nicotine (including substitution), as well as when they took any medication. On the last day of taking detoxification medication (or the next working day for outpatients where this falls on a weekend/public holiday), withdrawal, depressive and anxiety symptoms (PHQ-9: [37]; GAD-7: [38]) and sleep pattern will be recorded for all participants. Research participant satisfaction will be measured with the Client Satisfaction Questionnaire-8 (CSQ-8; [40, 41]). Any information not already obtained or previously available will also be completed and will include the following: using a semistructured questionnaire: years of GHB/GBL use, the amount of GHB/GBL used in the week prior to detoxification and the amount in a typical day/week, pattern of use, whether they are self-reported ‘dependent’ on any of these medication(s) that have been used to help self-treat or prevent previous withdrawal. Previous psychiatric and medical history, other drug or alcohol use including nicotine and determination of any dependence will be similarly established as well as using time-life follow-back, the alcohol screening questionnaire (Alcohol Use Disorders Identification Test (AUDIT); [42]) and appropriate parts of the mandatory Treatment Outcomes Profile (TOP; [43]) used in substance misuse services will be completed.

Regarding medication, the total amount of benzodiazepine prescribed, its dosing regimen and quantity taken will be recorded. Use of any other medication during the detoxification will also be recorded.

Any complications arising during preload or detoxification will be recorded. These will be classified as adverse events if they are not one of the following predetermined events which are known to occur in acute GHB/GBL withdrawal or detoxification: agitation or aggression, hallucinations (visual, auditory and/or tactile), tachycardia, seizures, ataxia, sedation, tremor and/or sweating. All adverse events occurring from the time a participant signs the Consent Form until completion of the last study-related procedure will be recorded in the Case Report Form. Any serious adverse event which occurs in a participant will be reported immediately to the chief investigator (CI) and sponsor and, if stated orally, will be followed by a detailed written report.

On day 30 after the start of detoxification (benzodiazepine detoxification, not preload), the researcher will contact the research participant to obtain information about any subsequent use of GHB/GBL, other recreational drugs/novel psychoactive substances/alcohol as well as any medication (prescribed or otherwise obtained) taken and psychosocial treatment/support received for their GHB/GBL dependence. In addition, any issues or events that could be related to their detoxification will be recorded.

Patients will be asked to return any remaining study medication to the clinic so that a pill count can be performed to assess compliance.

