### Data analysis

The primary focus of this study is to assess the feasibility of undertaking a definitive trial. In particular, we will characterise the optimal recruitment rate and strategies and characteristics of the proposed primary outcome measures (symptom severity, complications, and requirement for treatment escalation). The main analyses will be descriptive and provide estimates of variability and effect size with 95 % confidence intervals. This will include the rate of recruitment, the proportion of people approached who consent to randomisation, the proportion who complete detoxification and the proportion who will complete the follow-up assessment. We will also describe the distribution of scores on the primary outcomes and estimate the variance of the measure in this population. Data for our proposed secondary outcomes in the definitive trial will include change in anxiety, depression, sleep and quality of life as well as relapse to GHB/GBL use or change in other illicit drug or alcohol use 30 days after the start of detoxification. We will also identify appropriate criteria, e.g. benzodiazepine requirement or withdrawal score for minimisation or stratification in the full RCT.

We will use ANCOVA adjusting for patients’ characteristics and relevant clinical data. Where there is follow-up, methods applied to longitudinal data will be appropriate since they are able to detect significant differences between arms but they can also detect changes of the outcome measure(s) over time. We will also conduct an interim analysis to characterise the number of adverse events in each arm as described above.

An interim analysis to characterise the number of adverse events in each arm will also be conducted. Treatment escalation (i.e. admission to ICU for those presenting to the ED (unplanned) and admission to the general hospital for those in the Club Drug Clinic (planned)) will be closely monitored. From our clinical experience of complications from GHB/GBL withdrawal, if five individuals in any one group require treatment escalation, the sponsor and IDMEC will be immediately informed and recruitment suspended until there has been a discussion and consideration of the protocol and trial continuing. Stopping rules will also be agreed which specify the point at which interim results will be judged to be sufficiently conclusive for it to be appropriate for the IDMEC to recommend that they consider early termination of the trial.

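### Change in quality of life is listed as a secondary outcome, but Table 1 schedules no quality-of-life measure at two time points; four history and profile instruments also lack a baseline slot

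*Protocol article*

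**What the plan says.** Under Assessment and outcome measures, the article refers to Table 1 for the data that will inform the definitive trial's outcomes, and states that "the proposed secondary outcomes include change in anxiety, depression, sleep and quality of life". The Data analysis section repeats this: "Data for our proposed secondary outcomes in the definitive trial will include change in anxiety, depression, sleep and quality of life". Quality of life also appears as a secondary outcome measure under Primary and secondary objectives.

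Table 1 opens with a column headed "Baseline or as soon as data can be obtained", followed by daily columns, a final-day column, an ad hoc column and a day-30 column. Four rows carry a single tick, in the final-day column: "Lifetime GHB/GBL use questionnaire", "Time-life follow-back of alcohol and drug use", AUDIT and "Treatment Outcome Profile".

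The text after the table introduces the same items differently. At the end of detoxification, "Any information not already obtained or previously available will also be completed", and use history, follow-back, AUDIT and the relevant parts of the TOP are then listed. The Data analysis section says that the ANCOVA will adjust for patients' "characteristics and relevant clinical data" and names no variable.

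**The concern.** A change score needs the same instrument at two times. The other three change outcomes have that; quality of life has no named instrument at all. The study exists to supply estimates of variability and effect size for the proposed outcomes. One of those outcomes would come out empty, and the definitive trial would have nothing from this study on which to plan it.

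The second issue is timing. Years, amount and pattern of GHB/GBL use, recent substance use and AUDIT describe the participant at entry, yet the table gives them no entry slot. Anyone who disengages before the final-day visit may have none of them. Completing detoxification is itself one of the feasibility estimates, so this missingness could be related to outcome. The same section also hopes to identify stratification or minimisation criteria for the full trial. Such criteria must be obtainable before randomisation, and amount of use is an obvious candidate.

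**Working it through.** The article gives no figure to reproduce on this point, so the check is a count of scheduled time points per instrument, read from Table 1.

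| Item | Baseline | Final day | Day 30 | Change computable from the schedule? |
|---|---|---|---|---|
| PHQ-9 (depression) | yes | yes | no | yes |
| GAD-7 (anxiety) | yes | yes | no | yes |
| Sleep questionnaire | yes (and daily) | yes | no | yes |
| Named quality-of-life measure | none | none | none | no |
| TOP | no | yes | no | no |
| AUDIT | no | yes | no | no |
| Follow-back | no | yes | no | no |
| Lifetime GHB/GBL use | no | yes | no | no |

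1. **Quality of life.** Three of the four change outcomes have two scheduled measurements; quality of life has none. The account of the day-30 contact covers substance use, medication, support received and events linked to the detoxification, so it adds no quality-of-life measurement. Even if the TOP were meant to serve, it has one scheduled time point.

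2. **The four instruments against their neighbours.** The catch-up list in the text also contains psychiatric and medical history. Table 1 ticks those two in the baseline column and leaves use history, follow-back, AUDIT and TOP blank there. That column already allows for data that cannot be had at once, so an acutely unwell patient does not explain the difference.

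3. **Recovery later.** Participants who stop study medication stay in follow-up unless they withdraw consent. The day-30 column, however, holds only three follow-up questionnaires (GHB/GBL use, drug and alcohol use, service use). Someone who misses the final-day visit but is reached at day 30 has no scheduled occasion for the four instruments.

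4. **Planned group.** One history item is the amount used in the week before detoxification. In the planned group (60 of 88) that week includes the 2-day randomised preload. The Background reports that preloading seemed to help stabilise use before detoxification, so this item could be partly a post-treatment measurement. The Randomisation section puts the baseline assessment before allocation, so a baseline tick would avoid this.

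5. **Illustration only.** The article gives no early-leaver rate. Assume that a fraction d of the 60 + 28 = 88 participants miss the final-day visit, that none had these items recorded earlier, that the items are used as covariates, and that incomplete cases are dropped. Then 88 × d participants are lost, and interval width grows by 1/√(1 − d):
   - d = 0.10: 8.8, about 9 lost; 1/√0.90 = 1.054, about 5% wider
   - d = 0.20: 17.6, about 18 lost; 1/√0.80 = 1.118, about 12% wider
   - d = 0.30: 26.4, about 26 lost; 1/√0.70 = 1.195, about 20% wider

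   None of these assumptions is stated in the article. The figures show scale and are not an estimate.

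**The case against.** The strongest reply concerns the four instruments. A reader of Table 1 might infer that they are collected on the final day and at no other time, and that adjustment covariates will therefore be missing for everyone who leaves early. The article does not support that reading:

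- The text makes the final day a catch-up for whatever has not yet been obtained, which permits earlier collection.
- The covariates are not named, and naming them is commonly left to an analysis plan. Many candidates do have a baseline tick: CIWA-Ar, the Sedation Assessment Tool, PHQ-9, GAD-7, sleep, vital signs, psychiatric and medical history, concomitant medication, and daily drug, alcohol and nicotine use.
- Stopping study medication does not end follow-up, and nothing says that treatment escalation does.
- The use-history items are retrospective and can be asked late.

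All of this stands, and it reduces the covariate issue to a risk for those who disengage. It does not remove the gap: the text permits earlier collection, but the table does not schedule it.

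A reader might also infer that the TOP was meant as the quality-of-life measure. The article never says so. It describes the TOP as mandatory in substance misuse services and uses only parts of it. A routine earlier record may therefore exist, more plausibly for outpatients than for unplanned inpatients. That possibility is not a scheduled baseline, and it does not make the TOP the stated instrument.

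Finally, this is a descriptive feasibility study that aims to limit extra tests, so late completion of long questionnaires is defensible for patients in acute withdrawal. That argues for keeping the final day as a catch-up, not for leaving the baseline column blank. It also means that a day-30 quality-of-life measurement is optional: the 30-day time point attaches most naturally to relapse and substance use.

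**Conclusion.** The main point holds: the outcome list and Table 1 contradict each other. Followed as printed, the schedule cannot yield change in quality of life, one of four change outcomes, because no such measure is named or scheduled twice. This rests on the article alone and needs no assumption about dropout. Its weight is moderate, since it affects one secondary outcome in a feasibility study, but supplying estimates for the proposed outcomes is what the study is for.

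The second point holds in a smaller form. Use history, follow-back, AUDIT and TOP have no baseline or day-30 tick, so participants who disengage before the final-day visit have no scheduled collection of them, and the table should be brought into line with the text. Loss of covariates is a possible consequence of unknown size, because neither the covariates nor an early-leaver rate is given.

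**What to change.** - **Quality of life.** Name the measure and tick it in Table 1 at baseline and at one later visit, for example the final day as for PHQ-9 and GAD-7. Otherwise delete change in quality of life from Assessment and outcome measures and from Data analysis, and adjust the objective to match.
- **History and profile items.** Tick the lifetime GHB/GBL use questionnaire, follow-back, AUDIT and TOP in the baseline column, which already allows for delay when a patient is unwell. In the planned group, complete them before the preload where possible, and state which week the recent-use question refers to. Keep the final day as catch-up, as the text already provides.

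The cost is an edit to Table 1 and a longer first visit. The history and profile items need no new questionnaire. A quality-of-life measure would be an addition only if the study does not already hold one that it intends to use.

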Furthermore, our clinical experience of GHB/GBL withdrawal in outpatient settings has been that patients who slowly reduce their GHB/GBL use describe significant anxiety and cravings during the few days before commencing medically assisted detoxification. For some, this acted as a deterrent to attending for treatment and a trigger for using higher doses of GHB/GBL. Consequently, we have initially used baclofen 2 days prior to stopping GHB/GBL in a small number of patients. There was very positive feedback from patients regarding the benefit, particularly in terms of reduced cravings and helping to stabilise pre-detoxification GHB use. The use of baclofen in our outpatient clinical service prior to initiating medically assisted detoxification has now become more widespread. The 2 days of pre-detoxification ‘preloading’ of baclofen at a standard dose of 10 mg three times a day has not resulted in any clinical incidents in relation to baclofen. This preloading with baclofen has previously not been formally studied to determine the usefulness of baclofen itself, neither has whether some of the reported benefits relate more to engagement with drug treatment services pre-detoxification than to baclofen itself.

Baclofen has been licensed in the UK for many years for the treatment of spasticity (maximum, 100 mg per day) and can be safely prescribed to a wide range of patients (see Summary of Product Characteristics (SPC), https://www.medicines.org.uk/emc/medicine/23850). Our clinical experience is that it is associated with few side effects. Whilst a withdrawal state is recognised for baclofen, this is unlikely to occur with its use in acute GHB withdrawal due to the short duration (7 to 10 days) of baclofen use in this indication. We suggest that the risk of complications from baclofen withdrawal is considerably less than that of inadequately managed GHB/GBL withdrawal [15, 18]. Nevertheless, whilst the use of baclofen holds promise, there are potential adverse effects on cardiovascular, neurological and respiratory systems so controlled data is urgently required to determine its efficacy and safety in GHB/GBL withdrawal. Optimising outpatient treatment to reduce the risk of complications and hospital admission is important since many individuals decline admission [17, 25]. Despite this complexity and its impact on, and cost to, the individual and the NHS, there is limited knowledge about how to best treat people in planned or unplanned GHB/GBL withdrawal.

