### Randomisation

An assessment of eligibility will be made by a physician following discussion with the potential participant and review of the accessible medical records. For some participants wishing to participate in the study but where there is limited or no access to medical records, the individual will be included in the trial unless one or more of the eligibility criteria are known not to be met. Informed consent will be obtained by a member of the study team.

To be able to respond to the urgent needs of people who are at high risk of withdrawing from GHB/GBL in a timely manner, the study medication will be pre-packed and pre-randomised and stored at both study sites. Randomisation codes in blocks of 4 (for the planned withdrawal group) and blocks of 15 (for the unplanned withdrawal group) will be generated by the trial statistician. Those eligible for inclusion will be randomised to baclofen or placebo by taking the next lowest consecutively numbered pack from storage cupboards in the respective treatment centre.

If eligible, have given informed consent and following baseline assessment, the participants are allocated as follows (see Fig. 1a and b). Those in the planned arm will receive a preload before their detoxification proper and will be allocated to one of three groups: preload of placebo (one tablet three times a day) followed by the benzodiazepine GHB/GBL detoxification regimen with the study medication, baclofen (10 mg three times a day) or placebo (one tablet three times a day) for up to 10 days, or preload of baclofen (10 mg three times a day) followed by the benzodiazepine GHB/GBL detoxification regimen with baclofen (10 mg three times a day) for up to 10 days. Those in the unplanned arm will receive their benzodiazepine detoxification regimen for GHB/GBL withdrawal with the study medication, baclofen (10 mg three times a day) or placebo (one tablet three times a day) for up to 10 days. In both unplanned and planned GHB/GBL withdrawal, clinicians will use the benzodiazepine and dosing regimen that they consider appropriate. The study medication will be discontinued at the same time as the benzodiazepine, with the decision about when both medications are to be discontinued made by their clinician.

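### PHQ-9 and GAD-7 are rated only once after baseline, on a clinician-decided day that varies between participants, and the existing day-30 contact omits both scales

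*Protocol article*

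**What the plan says.** Table 1 marks PHQ-9 and GAD-7 twice each: at baseline and at the end of detoxification. Neither scale is marked in the daily columns or in the 30-day column. The text of Assessment and outcome measures agrees and places the second rating "On the last day of taking detoxification medication", moved to the next working day for outpatients if needed.

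The calendar day of that rating is not fixed. Under Randomisation, "The study medication will be discontinued at the same time as the benzodiazepine". It is the treating clinician who settles when that happens. The benzodiazepine course is also open: "clinicians will use the benzodiazepine and dosing regimen that they consider appropriate". Study medication has an upper limit but no stated minimum, for example "followed by the benzodiazepine GHB/GBL detoxification regimen with baclofen (10 mg three times a day) for up to 10 days". The Background speaks of "due to the short duration (7 to 10 days) of baclofen use in this indication".

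A contact at a fixed distance from the start of benzodiazepine detoxification already exists. On day 30, "the researcher will contact the research participant to obtain information about any subsequent use of GHB/GBL", together with other substance use, medication, support received and events that may relate to the detoxification. No anxiety or depression score is listed there.

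Assessment and outcome measures and Data analysis both name change in anxiety and in depression among the secondary outcomes proposed for the definitive trial. Data analysis says the study is to supply effect sizes, with confidence intervals, and estimates of spread.

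**The concern.** The only follow-up score for these two outcomes falls on a day that is set after randomisation, by a decision that the randomised treatment could influence. The trial rests on the hypothesis that baclofen eases withdrawal, so a difference between arms in detoxification length is plausible. Anxiety and depression scores probably move during those days. If the arms are rated at different average times, part of any difference in change reflects when people were rated. Blinding does not prevent this, because the timing would itself be a consequence of treatment.

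Two products of the feasibility study would be affected: the effect size for change in anxiety and depression, and the SD that would be carried into planning the definitive trial. An analysis plan could report the rating day or adjust for it, although it is a post-randomisation variable. It could not supply a fixed-time score that the schedule never collects.

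**Working it through.** **The plan's own figures.** The document gives no power, SD or effect size for these scales, so there is no figure to reproduce. The recruitment total adds up: 60 + 28 = 88.

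**What follows from the text alone.**
1. There is one post-baseline rating per scale (Table 1 and the text agree).
2. Its day is the last medication day, decided by the clinician, with a 10-day limit on study medication (Randomisation).
3. Outpatients whose last day is a weekend or public holiday are rated later. A Saturday finish is rated on Monday, 2 days on.
4. So the time from start of detoxification to rating varies between participants. On the Background figure of 7 to 10 days, medication-end days alone would span 10 − 7 = 3 days.
5. Whether the arm means differ in timing does not follow from the text. That requires a treatment effect on duration.

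**Illustration A: common linear fall, no true effect at any fixed day (all inputs assumed).** Let scores fall by b points per day and let the mean rating day differ by d days between arms. The spurious difference is b × d.

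| b (points/day) | d = 0 | d = 1 | d = 2 | d = 3 |
|---|---|---|---|---|
| 0.25 | 0 | 0.25 | 0.50 | 0.75 |
| 0.5 | 0 | 0.5 | 1.0 | 1.5 |
| 1.0 | 0 | 1.0 | 2.0 | 3.0 |

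The first column is the important one: with equal mean duration, the bias in the arm difference is zero.

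**Illustration B: extra variance when mean duration is equal.** Suppose rating days 7, 8, 9 and 10 are equally likely and independent of the score. Their variance is (4² − 1)/12 = 1.25. The variance added to the score is b² × 1.25. With an assumed SD of 5 (variance 25) and b = 1.0, the SD becomes √(25 + 1.25) = 5.12. With b = 0.5 it becomes √(25 + 0.3125) = 5.03. The inflation is small. If the rating day is related to the score, the SD could move either way.

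**Illustration C: stopping tied to the score (assumed, not stated in the document).** Simulation with 200,000 per arm: baseline mean 14 (SD 4), daily noise SD 2, scores limited to 0 to 21, falls of 0.7 (placebo) and 1.0 (baclofen) points per day, and stopping between days 4 and 10 at the first score of 7 or less, otherwise at day 10.

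| | Placebo | Baclofen | Difference |
|---|---|---|---|
| Mean stop day | 7.8 | 6.9 | 0.9 |
| Mean score at stop day | 7.52 | 5.97 | 1.55 |
| Mean score at fixed day 7 | 9.13 | 7.13 | 2.00 |

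The stop-day difference is smaller by 2.00 − 1.55 = 0.45 points, or 0.45/2.00, about 22%.

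**Scale for comparison.** The 95% half-width is 1.96 × SD × √(2/n). With an assumed SD of 5 and equal groups (60/3 = 20 and 28/2 = 14, equal allocation also being an assumption), it is 1.96 × 5 × √(2/20) = 3.1 points and 1.96 × 5 × √(2/14) = 3.7 points. The 0.45-point shift is well inside both, and even the largest entry in Illustration A, 3.0, does not exceed them.

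**The case against.** The strongest case for the plan has four parts.

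- **The time point is legitimate.** For a drug given alongside detoxification, the state at the end of detoxification is a natural question. This stands, and the score should remain an outcome.
- **Day 30 asks a different question.** Study drug has been stopped for 30 − 10 = 20 days or more by then. Scores would also reflect relapse, other drug use and later support, and some participants will not be reached. This stands too. A day-30 score can supplement the end-of-detoxification comparison but should not replace it.
- **Little depends on these scales here.** They are secondary, the main analyses are descriptive, the article stresses a pragmatic design with few added tests, and the timing effect is likely to be small beside the confidence interval. This limits the weight of the point but does not remove it, because the estimates are meant to inform a later trial.
- **The analysis plan may deal with assessment day.** It may, and medication timing and quantities are recorded, so duration can be described. But Table 1 is explicit row by row, and no analysis can recover an unscheduled score.

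A reader might infer that the clinician stops treatment according to response, so that everyone is rated once judged well enough. The article does not say so. It names who decides and gives no criterion, and the section on study medication discontinuation allows study drug to stop for adverse events or at the participant's wish.

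A reader might also take the 4–5 days mentioned in the Background as the earliest stopping day. That figure is how long baclofen was given at the start of detoxification in an uncontrolled case series. It is not a stopping day in this trial.

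**Conclusion.** The point holds as a modest design weakness. It is certain from the document that PHQ-9 and GAD-7 are rated once after baseline, on a day that varies between participants, and that the fixed day-30 contact collects neither scale. It is conditional that the comparison of arms is distorted: this requires baclofen to change mean detoxification length. If it does, the timing effect may create, inflate or mask a difference. If it does not, the varying day mainly adds variance to the pilot SD, and on the assumptions shown that addition is small.

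The document supports no numerical size. The illustrations rest entirely on assumed slopes, durations, SD and stopping rule, and serve only to show direction and order of magnitude.

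Two wider readings are not supported. The first is that the arms are bound to be compared at different times; that is certain only for individuals. The second is that CIWA-Ar and sleep share the fault; both are rated daily, Data analysis provides for longitudinal methods, and nowhere does the article say that arms will be compared on the last-day value.

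**What to change.** Add PHQ-9 and GAD-7 to the day-30 contact, both in Table 1 and in the text, as an additional measure at a fixed time from the start of detoxification. Keep the end-of-detoxification score as an outcome. Record the day of that assessment, counted from the start of detoxification, and report its distribution by arm, so that a reader can see whether timing differed.

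While editing, make clear which secondary outcomes the 30-day phrase in Assessment and outcome measures and in Data analysis covers. The sentence can be read as including anxiety and depression, which Table 1 does not schedule then.

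The cost is two short questionnaires at a contact already planned, using scales the article describes as already in routine clinical use, with no extra visit. The downsides are some loss to follow-up at day 30 and scores that will partly reflect relapse and treatment received after detoxification, so the report should interpret them in that light. A feasibility study is a good place to learn how completely such scores can be collected. No change to the clinical decision on stopping medication is proposed.
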